## Abstract

Women who received a diagnosis of breast cancer often report impairments in physical and psychological wellbeing, even some years after treatments. Individual awareness about physical changes, body image, and current sensations related to their body is important to maintain a psycho-emotional balance. Virtual reality, as an advanced human–computer interface, can be an effective tool to improve breast cancer survivors' abilities to know and manage their current sensations related to their bodies. The present study protocol proposes a virtual reality intervention aiming at promoting interoception and emotional wellbeing, fear of cancer recurrence, and body perception in breast cancer survivors, according to the three data collection times. Repeated-measure analysis of variance (ANOVA) with between–within interaction will be performed. Expected results include participants' awareness of their internal feelings, the reduction of negative emotions, and the management of symptoms related to the body, clarifying characteristics for the effective implementation of VR psychological intervention in the future.

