### Procedure and measures

The study duration will be ~12 months, from recruitment until the conclusion of T2. Researchers will contact various breast cancer patient associations to share the current project and promote contact with interested people. Women interested in participating in the present research project can contact the researchers by writing to the email address provided by the association. The study will also be publicized through social networks (e.g., Facebook, LinkedIn, and Instagram), inviting interested women to contact the researchers through the email indicated in the study announcement. No monetary compensation will be provided, and mandatory adherence to the study will be requested as informed consent before administering the questionnaires. It will be made clear that participation in the research is completely free, voluntary, and free of charge. All participants will have the option to discontinue the research at any time without providing any explanation. At the end of the VR intervention, participants will be asked for their willingness to provide a personal contact that will be exclusively used to send them the follow-up questionnaires after 1 month (T2). Regarding the questionnaires, a code will be assigned to make the collected data pseudonymized.

The study will be conducted following the Declaration of Helsinki principle and informed written consent will be collected from all participants. The study protocol has been revised and approved by the Ethical Committee of the University of Milan.

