## Data analysis and sample size estimation

An *a priori* estimation of the sample size required for the present study was calculated using G*Power 3.1.9.2 software (Faul et al., 2007) to analyze variance with repeated measure (ANOVA) with between–within interaction. The primary endpoint will be the difference between the two experimental groups (i.e., between-subject factor) in the improvement of the overall MAIA scale score at pre- (T0), post-intervention (T1), and follow-up (T2) times. To detect a weak-median effect size (i.e., partial η^2^ = 0.04), the required sample size is 40 (i.e., 20 participants in each group). The type-I error rate (α) was set at 0.05 (two-sided), and the power (1 – β) was set at 0.90. The collected data could be analyzed using a statistical analysis software, the Statistical Package for Social Science (SPSS, version 27.0).

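### The planned repeated-measures ANOVA, in its standard form, would discard the observed T0 and T1 scores of any woman without a T2 questionnaire; a mixed model would keep them

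*Protocol article*

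**What the plan says.** The Abstract of the protocol article commits to the method: "Repeated-measure analysis of variance (ANOVA) with between–within interaction will be performed". The section on data analysis and sample size estimation ties it to the primary endpoint, the group difference in improvement of the "overall MAIA scale score at pre- (T0), post-intervention (T1), and follow-up (T2) times". The same section sizes the trial for that test: "To detect a weak-median effect size (i.e., partial η^2^ = 0.04), the required sample size is 40 (i.e., 20 participants in each group"), and "The type-I error rate (α) was set at 0.05 (two-sided), and the power (1 – β) was set at 0.90". The software sentence is more tentative ("The collected data could be analyzed using a statistical analysis software") and names SPSS 27.0.

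Two statements under Procedure and measures bear on how complete T2 will be. After the session, "participants will be asked for their willingness to provide a personal contact that will be exclusively used to send them the follow-up questionnaires" one month later. And "All participants will have the option to discontinue the research at any time without providing any explanation". No payment is offered. The article states no dropout rate and no allowance for dropout in the 40.

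**The concern.** A three-wave repeated-measures ANOVA works on each woman's complete T0–T1–T2 record. SPSS GLM Repeated Measures deletes listwise, so a missing T2 score removes the whole woman, including the two MAIA scores already collected around the session.

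The design makes such records likely. T2 depends on a second agreement, given after allocation and after the woman has been through her assigned session, and is then answered remotely a month later.

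Two things are at stake. With 20 women per arm, every lost record costs power. And because the second agreement follows treatment, T2 return could be related to how a woman responded, so the completers may not represent the women randomised.

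**Working it through.** **Inputs from the article:** 2 groups, m = 3 time points, partial η² = 0.04, α = 0.05, power 0.90, N = 40.

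**Assumptions (not in the article):** correlation ρ between time points, sphericity parameter ε = 1 for the power figures, and proportion d without T2.

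**Formula** (noncentral F for the group × time interaction, as in G*Power):
- f² = 0.04/0.96 = 0.0417, so f = 0.204
- λ = N·m·f²/(1 − ρ)
- df1 = (2 − 1)(3 − 1) = 2 and df2 = (N − 2)·2

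**Step 1: the plan's own figure.** With ρ = 0.5, λ = 40 × 3 × 0.0417/0.5 = 10.0, df2 = 76, and power is 79.9%; 90% would need N = 54. The stated 90% at N = 40 is reached with ρ of about 0.62: λ = 5/0.38 = 13.2. Whether 40 was correctly derived is a separate question. Both values of ρ are carried forward so that this point does not depend on the answer.

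**Step 2: power when women without T2 are dropped.**

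| Missing T2 (assumed) | Women analysed | Power, ρ = 0.62 | Power, ρ = 0.5 |
|---|---|---|---|
| 0% | 40 | 90% | 80% |
| 10% | 36 | 86% | 75% |
| 20% | 32 | 82% | 69% |
| 30% | 28 | 76% | 63% |

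Example for 20%: N = 32, df2 = 60, λ = 4/0.38 = 10.5 or 4/0.5 = 8.0. To end with 40 complete records, enrolment would have to be 40/(1 − d) = 45, 50 or 58 for d = 10, 20 or 30%.

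**Step 3: bias.** These are illustrative simulations, with MAIA in SD units and correlations of 0.8 (T0–T1) and 0.5 (each with T2).
- No true effect, T2 return depending on the T1–T0 change in one arm only, about 78% retained: the completer between-group difference in change from T0 is about +0.17 SD at T1 and +0.09 SD at T2. A likelihood analysis using all observed T0 and T1 values gives about 0 at both.
- Same dependence in both arms: no bias under no effect, but a true 0.30 SD shrinks to about 0.24 at T1 and 0.27 at T2.
- T2 return depending only on baseline MAIA, equally in both arms (about 27% missing): no bias.

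**Step 4: sphericity (secondary).** T2 comes a month after a T0 and T1 that appear to fall in one visit, so a higher T0–T1 correlation is plausible. Assumed correlations for T0–T1/T0–T2/T1–T2 of 0.85/0.60/0.60 give ε = 0.78 and an uncorrected type I error of about 6.0%. With 0.90/0.60/0.65, ε = 0.70 and the error is about 6.7%. In simulations over similar patterns, the Greenhouse-Geisser correction brought it back to about 4.7–5.0%.

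**The case against.** The strongest reply is that the article names an ANOVA and nothing more. It does not mention completers, listwise deletion or an analysis set, and a full analysis plan could add imputation. That stands in part: a reader might infer that the sponsor has decided to exclude women without T2, and the article does not say so. What it does fix is a method whose standard form has this consequence. The point is about that choice and not about missing detail.

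Three stronger readings are tempting and not supported.
- *That the ANOVA is valid only if dropout is completely at random.* Too strong: return depending on baseline alike in both arms left the group comparison unbiased.
- *That sphericity will be violated and type I error inflated.* The article gives no correlations, does not state outright that T0 and T1 fall in one visit, and nowhere says the test will be uncorrected. Greenhouse-Geisser results are routine SPSS output.
- *That power falls from 80% to 69%.* This takes ρ = 0.5 and 20% loss as given. The starting value of 80% belongs to the separate sample size question.

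It is also fair that the Participants section calls 40 a minimum, so over-recruitment could offset some loss. And the mixed model does not always recover the power. By an information-based calculation at ρ = 0.5 and 20% missing T2, it reaches about 76–78% against 69% if the effect is already present at T1, but only 69–71% if the effect appears at T2 alone.

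**Conclusion.** The concern holds in this form: the chosen primary analysis, as normally run, throws away observed primary-endpoint data in a situation that the recruitment and follow-up procedure makes foreseeable.

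Measured against the article's own 90% (ρ = 0.62, ε = 1), the type II error rises from 10% to about 14%, 18% and 24% with 10, 20 and 30% missing T2. The dropout range and both correlations are assumptions. Bias is possible rather than demonstrated. It requires T2 return to depend on the response at T1, and under no true effect it arose only when that dependence differed by arm.

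Sphericity is a side issue, worth one or two percentage points of type I error under assumed correlations, and would not justify a change alone. This is a change that should be made; it does not invalidate the trial.

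**What to change.** Name as primary analysis a linear mixed model for repeated measures of overall MAIA: SPSS MIXED, REML, time as a categorical factor, unstructured 3 × 3 covariance, Satterthwaite degrees of freedom, fixed effects for group, time and group × time. Include all randomised women as allocated, with every available MAIA value. Keep the completer ANOVA, Greenhouse-Geisser corrected, as a sensitivity analysis. State the expected proportion without T2 and allow for it in the recruitment target.

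The model change costs analysis wording and slightly more analysis work in the software already named. It tests the same interaction and does not need sphericity. It does assume that T2 is missing at random given the observed scores, and it recovers little power if the effect appears only at T2, which is why the recruitment allowance is still needed. On the assumed range, that allowance is 5 to 18 women above 40.

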## Introduction

Body image (BI) is defined as the internal representation of one's outward appearance (Thompson et al., 1999), also including its related emotions and thoughts (Lewis-Smith et al., 2018; Sebri et al., 2020). BI involves perceptual (e.g., accuracy in estimating one's body), affective (feelings and emotions), attitudinal (the degree of satisfaction related to one's body), cognitive (beliefs and thoughts), and behavioral (e.g., possible compensatory behaviors enacted to achieve a satisfactory self-image) levels (Cash and Smolak, 2011). Considering the malleability of the self [It is conceptualized as a function of social and cognitive contexts demonstrating that mood can lead to temporary changes in the self (Markus and Kunda, 1986; Markus and Nurius, 1986).] and the motivation dynamics after cancer (Durosini et al., 2021), significant and/or traumatic events (such as an oncological experience) can affect BI strongly (Sebri et al., 2020). The literature highlights that women with previous breast cancer experience may live with negative emotions that affect their quality of life (Durosini et al., 2022) and develop a negative BI due to physical and psychological issues after diagnosis and oncological treatment and interventions (Maass et al., 2015; Sherman et al., 2018). In BI evaluation, inner sensations and related awareness play a relevant role. Particularly, breast cancer survivors may perceive bodily sensations never felt before, increasing interoceptive awareness, especially about the breast(s) (Paterson et al., 2016). As a definition, interoception refers to the ability to be aware of one's internal sensations, such as itching and hunger. The debate about the role of interoception awareness and its impact on emotions is ongoing. On the one hand, literature has stated that such awareness is important to regulate internal states and maintain a psycho-emotional balance (Herbert and Pollatos, 2012), promoting emotional regulation and positive overall self-representation and self-appraisals. On the other hand, being aware of interoception and its related inner sensation could increase the focus on internal sensations as it is linked to the fear of cancer recurrence. Controlling behaviors, such as constantly looking for breast lumps, may frequently emerge increasing negative emotions, such as distress and anxiety (Humphris and Ozakinci, 2008). Thus, effective psychological intervention to promote an effective awareness of the interplay between internal and external sensations is crucial to increase recognition and acceptance of the body and its related inner sensations after illness, without increasing negative emotions (Raimo et al., 2021; Sebri et al., 2022). In other words, increasing interoceptive capacity can, therefore, support women in recognizing their feelings and regulating related emotions (Reed et al., 2016; Czamanski-Cohen et al., 2019). Additionally, following Higgins' discrepancy theory (Higgins et al., 1985), the cognitive dissonance between current and ideal self-images could induce concerns and discomfort related to BI, with important consequences on emotions (anxiety and depression in particular), quality of life, and social relationships. Accordingly, the perception of the stigma as a “patient” referring to illness characteristics could decrease individuals' empowerment, improving shame and social isolation (Amini-Tehrani et al., 2021; Brunet and Price, 2021).

Virtual reality (VR), as a tool that allows users to experience a sense of belonging with a body in a virtual world (*virtual reality full body illusion*), is generally involved in promoting body awareness and regulation of emotional wellbeing, especially in the eating disorder fields (Slater et al., 2008; Serino et al., 2016; So et al., 2022). Starting with the process of embodiment and the sense of presence, users can, therefore, perceive their real and virtual bodies simultaneously (Ventura et al., 2018). Such an experience of the virtual body belonging is the result of the combination of visual and tactile stimulations and individuals' ability to identify their own body (*self-identification*) that occupies a specific space (*self-location*) and its related internal sensations (Haugstad et al., 2006; Moussally et al., 2017; Nakul et al., 2020).

In accordance with the present theoretical framework, it might be interesting to investigate the VR application aiming at improving BI awareness and wellbeing in women who received a cancer diagnosis. The overall purpose of this research protocol was to implement a VR intervention to improve interoceptive ability and emotional wellbeing in breast cancer survivors. Specifically, the objectives of the present protocol study are to evaluate the impact of the following:

- Sensation manipulation to promote interoception awareness and psychological wellbeing, positive self-appraisals, and emotional regulation (reducing, for example, the fear of cancer recurrence) through VR;- A VR intervention on body awareness and negative body sensations following illness, addressing interoceptive sensations related to the body.

We expect that the present study focusing on VR intervention may help women with a history of breast cancer to improve their psychological wellbeing and awareness of inner sensations, promoting better emotional regulation.

## Methods

### Participants

Women who have experienced breast cancer in the past and that have completed cancer treatments will be included in this study. Specifically, inclusion criteria are as follows: (a) adult women (18 years and older); (b) women who have previously received a diagnosis of breast cancer (stage I and II); (c) women who have received cancer treatment (e.g., chemotherapy, radiotherapy, or monotherapy) in the past. Contrarily, exclusion criteria include people with a diagnosis of metastatic cancer and women who are unable to sign an informed consent and/or have poor knowledge of the Italian language. A sample size of at least 40 participants (please see “Data Analysis and Sample Size Estimation” section) is estimated to be involved.

### Procedure and measures

The study duration will be ~12 months, from recruitment until the conclusion of T2. Researchers will contact various breast cancer patient associations to share the current project and promote contact with interested people. Women interested in participating in the present research project can contact the researchers by writing to the email address provided by the association. The study will also be publicized through social networks (e.g., Facebook, LinkedIn, and Instagram), inviting interested women to contact the researchers through the email indicated in the study announcement. No monetary compensation will be provided, and mandatory adherence to the study will be requested as informed consent before administering the questionnaires. It will be made clear that participation in the research is completely free, voluntary, and free of charge. All participants will have the option to discontinue the research at any time without providing any explanation. At the end of the VR intervention, participants will be asked for their willingness to provide a personal contact that will be exclusively used to send them the follow-up questionnaires after 1 month (T2). Regarding the questionnaires, a code will be assigned to make the collected data pseudonymized.

The study will be conducted following the Declaration of Helsinki principle and informed written consent will be collected from all participants. The study protocol has been revised and approved by the Ethical Committee of the University of Milan.

Before VR intervention, participants will be randomized into the two research groups through Excel software (RAND function). Women in the experimental group will be invited to wear a 3D oculus and follow specific steps of the present intervention. Specifically, women will be shown a female avatar. The proposed virtual environment will be located in a neutral room, and the avatar will have an average body size compared to the general population. Women will be able to see the avatar's entire body looking straight ahead through the use of a 3D oculus. Then, visual and auditory stimuli will allow for an increased sense of belonging with respect to the virtual body, as described by Slater et al. (2008). To sum up, the intervention will consist of viewing a silhouette of a body through VR and following a series of visual and auditory stimuli to improve their abilities to perceive and control internal sensations through VR, whereas participants included in the control group will be asked to wear a 3D oculus for VR viewing. Unlike the previous group, participants will be invited to observe an immersive experience for relaxation purposes as a neutral stimulus. The relaxation experience related to the control group will last the same time as the intervention experience for the experimental group. Breast cancer survivors who will belong to the control group will not receive different instructions in terms of VR characteristics and how to use it.

More specifically, the proposed intervention will be structured as follows:

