#### Phase 2 (T1)

Subsequently, participants will be randomly divided into the experimental and control groups. Participants in the experimental group will be asked to sit on a chair and place their open palms on the table without crossing their legs and keeping their backs straight. Wearing 3D oculus and donning the sensor, the participants will be immersed in VR where they will see the virtual body of an avatar positioned in the same position as them. The experiment will begin with an initial warm-up phase in which participants will be allowed to stand in the virtual environment without receiving additional stimuli (2 min). In this first phase, psycho-physiological indices (heart rate and heart rate variability) will be measured using wearable sensors at the wrist so as not to interfere with the session. Next, the experimental group will observe via VR visual stimulation on different parts of the virtual body (breasts, fingers, and toes) and listen to vocal stimulation, in a consecutive and randomized manner among the group participants. Specifically, this intervention will be structured as follows: The participants will see a light on their virtual body that, starting from an iridescent red color, will fade slowly, becoming white. At the same time, an external voice will guide the participants toward a gradual decrease in sensations of discomfort and itching, in a combination of the visual stimuli. This treatment will initially be proposed for a total of 5 min, considering that 90 s is sufficient to induce body illusion. This process will be proposed in the same mode (duration equal to 5 min) for the body parts of interest of the same (breasts, fingers, and toes), with a 2-min break between stimulations. During the breaks, participants will remain immersed in VR, without additional stimulation. In contrast, participants assigned to the control group, once immersed in a VR depicting a natural environment, will hear only a guiding voice reading a script aimed at relaxation. Once the experiment is over, all participants will fill out the battery of post-intervention questionnaires, which includes the following:

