#### Phase 3 (T2)

Lastly, a final administration of questionnaires will be conducted 1 month after the end of the intervention. Specifically, in this phase, the *Multidimensional Assessment of Interoceptive Awareness* (MAIA), the *State-Trait Anxiety Inventory* (STAI-Y1), the *Self-Assessment Manikin* (SAM), and the *Checking behaviors*, the *Cancer Worry Scale* (CWS) will be administered to participants (see Figure 1).

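### The contact needed for T2 is requested only after the VR session, so entry to follow-up is a second opt-in that can cause arm-related loss at T2

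*Protocol article*

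**What the plan says.** The order of events can be read from the protocol article.

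- **Consent.** Under Procedure and measures, "mandatory adherence to the study will be requested as informed consent before administering the questionnaires". Phase 1 (T0) also places signing before the first battery.
- **Randomisation.** "Before VR intervention, participants will be randomized into the two research groups" (Procedure and measures).
- **Session.** In Phase 2 (T1), the experimental arm sees a light on an avatar's breasts, fingers and toes while a voice guides a decrease in discomfort and itching. "In contrast, participants assigned to the control group, once immersed in a VR depicting a natural environment, will hear only a guiding voice" reading a relaxation script.
- **T2 contact.** "At the end of the VR intervention, participants will be asked for their willingness to provide a personal contact" (Procedure and measures). The same sentence limits that contact to sending the one-month questionnaires. No other route to T2 is described.
- **T2.** "a final administration of questionnaires will be conducted 1 month after the end of the intervention" (Phase 3). It covers MAIA, STAI-Y1, SAM, checking behaviours and CWS. Of these, only MAIA is in the T1 battery.
- **Primary endpoint.** The difference between groups in improvement of the "overall MAIA scale score at pre- (T0), post-intervention (T1), and follow-up (T2) times" (Data analysis and sample size estimation).

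The article gives no expected T2 opt-in rate and no allowance for loss.

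**The concern.** Randomisation makes the two groups comparable at T0. That comparability carries over to T2 only if reaching T2 does not depend on the arm and on matters related to outcome. Here the gate to T2 stands directly after the session. A woman decides whether to leave a contact when her reaction to her own arm is freshest, and the arms differ in content. The Introduction itself notes that attention to inner sensations is linked to fear of recurrence and may increase distress and anxiety, so a reaction that differs by arm and is tied to the outcomes is plausible.

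Two things are at stake. For MAIA, a repeated-measures ANOVA restricted to women with all three times would also discard the T1 values of those who decline T2. For anxiety, fear of recurrence, SAM and checking behaviours, T2 is the only post-baseline value, so the comparison between arms rests wholly on those who opted in.

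The exposure is avoidable. Women already write to the researchers by email and sign consent before T0, and the questionnaires are coded rather than anonymous.

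**Working it through.** The documents give no figure for T2 opt-in, so every rate and correlation below is an assumption. The calculations show what the mechanism can do, not what it will do.

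**Illustration A: refusal depends on MAIA improvement by T1**

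Assumptions: no true effect; MAIA standardised to SD 1 at each time; correlation 0.85 between T0 and T1, and 0.60 between T2 and each of the others; a fraction q refuses T2 in each arm. In the experimental arm the refusers are those with the smallest T1-T0 change; in control they are random.

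1. SD of T1-T0 change = √(2(1 − 0.85)) = √0.30 = 0.548.
2. Mean standardised T1-T0 change among those who stay = φ(z_q)/(1 − q). At q = 0.20 this is 0.280/0.80 = 0.350.
3. Completer bias in T1-T0 = 0.350 × 0.548 = 0.19 SD.
4. Cov(T2-T0, T1-T0) = 0.60 − 0.60 − 0.85 + 1 = 0.15.
5. Completer bias in T2-T0 = 0.350 × 0.15/0.548 = 0.096, about 0.10 SD.

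| Refusal per arm | T1-T0 bias, completers | T2-T0 bias, completers |
|---|---|---|
| 10% | 0.11 SD | 0.05 SD |
| 20% | 0.19 SD | 0.10 SD |
| 30% | 0.27 SD | 0.14 SD |

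**Where this bias comes from**

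- Cov(T2, T1-T0) = 0.60 − 0.60 = 0, so the completers' T2 level is not shifted.
- Cov(T0, T1-T0) = 0.85 − 1 = −0.15, so the completers' T0 mean is shifted by −0.15 × 0.350/0.548 = −0.096.

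The T2-T0 bias is thus an imbalance in observed baseline. Selection depends only on T0 and T1 MAIA, which are scheduled for every participant. Regressing T2 on T0 and T1 in completers and averaging the prediction over all randomised women gave a T2-T0 bias of about 0.00 at 20% refusal (simulation, 1,000,000 draws).

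**Illustration B: refusal depends on an unrecorded reaction to the session**

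Assumptions: no true T2 effect; a standard normal reaction score correlates r with the T2 outcome; the women with the best reactions opt in, a proportion p in each arm. Bias = r × the difference between arms in mean score among those retained.

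- At p = 0.70 the mean is 0.497; at p = 0.90 it is 0.195; the difference is 0.302.
- r = 0.3 gives 0.09 SD; r = 0.5 gives 0.15 SD.
- The apparent advantage goes to the arm that loses more women, so the sign reverses if control loses more.
- If opt-in and its determinants are the same in both arms, or if r = 0, the bias is 0.

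**T2-only outcomes**

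STAI-Y1, SAM, CWS and checking behaviours have T0 values but no T1 value, so the adjustment that works in Illustration A has no counterpart on their own scale. T1 MAIA, satisfaction and the ITC-SOPI could serve as auxiliary variables. They help only so far as they explain both the opt-in and the T2 outcome.

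**The case against.** Much of the case on the other side stands.

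- **Consent is not late.** It is signed before T0 for a study that runs to the end of T2. A reader might infer that permission for follow-up as a whole is postponed. The text supports less: only the contact, and willingness to give it, come after the session.
- **Bias is possible, not shown.** A reader might infer that T2 is biased. Both arms wear the same headset for the same time, and no opt-in rate or difference between arms is given.
- **The MAIA illustration does not show irreparable bias.** A reader might infer that analysis cannot repair the loss. Illustration A shows the reverse when refusal depends on observed MAIA, and missing-data handling may be in an analysis plan not shown. The 0.19 SD in T1-T0 arises only if women are deleted at T1 because T2 is missing.
- **Illustration A is an extreme.** If the refusal score correlates only 0.3 to 0.5 with T1-T0 change, the T2-T0 bias at 20% refusal is 0.096 × 0.3 = 0.03 to 0.096 × 0.5 = 0.05 SD. Even in the extreme case, the type I error of a T2-T0 comparison with 16 per arm was 6.0% against 5%.
- **Some loss would remain.** Women may stop at any time, or not answer a questionnaire sent a month later, for the same reasons.
- **Power is a separate matter.** A fall from 80% to 69% at 20% loss (40 to 32 women) holds for a correlation of 0.5, which the article does not state. At 0.65, which is closer to the stated 90% power with 40 women, it is 92% to 85%.

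None of this removes the point. Staying in follow-up unless one withdraws is different from having to opt in again straight after the assigned session, and that second gate is a stated procedure, not a detail lost in condensing the article.

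**Conclusion.** The concern holds as a design weakness. As written, the plan opens an avoidable route to arm- and outcome-related loss at T2, a time that belongs to the primary endpoint and is the only post-baseline measurement of four secondary measures. The documents do not support saying that T2 will be biased, in which direction, or by how much.

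Under the assumptions of Illustration A, the complete-case T2-T0 bias in MAIA is about 0.10 SD at 20% refusal, and it largely disappears in a likelihood-based analysis using all T0 and T1 MAIA values. The weaker position is that of the T2-only outcomes, where that repair is not available on the outcome's own scale. Under Illustration B, with opt-in of 70% against 90%, the spurious difference would be 0.09 to 0.15 SD. The change is worth making because it costs little, not because a large bias has been shown.

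**What to change.** In Procedure and measures and in the consent form:

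1. Collect the T2 contact, and agreement to be contacted at one month, with the informed consent before randomisation, from all participants. Store the contact apart from the coded data.
2. Send T2 to every randomised woman unless she has withdrawn.
3. Report T2 completion by arm.

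The cost is one revised consent and procedure paragraph and a minor ethics amendment, with no added visit or measure. Withdrawal and non-response after the session remain possible, so the change removes one exit point and not all loss.
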